## 12 ACCESS TO SOURCE DATA

Principal investigators have permission from the head of the clinical department to peruse and monitor hospital case records of enrolled infants and their mothers, and this will also be explained to parents in the informed consent interview.

## 13 QUALITY CONTROL

### 13.1 Source data

The major part of data collected is clinical in nature, which is found in the hospital case record, this is the primary data source. Investigator is responsible to ensure that the source of all data collected is recorded and can be retrieved. The cardiorespiratory parameters for the SCRIP score are collected more frequently than clinical routine and will therefore be collected on paper. This applies also to questionnaires and interview guide sheets. Various samples will be analyzed and results will come from different laboratories.

The subject's hospital case record will include a note as to the infant's participation in the study, the study name, the allocation arm, study ID number and contact persons for study.

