### **8.7 Blinding and breaking code**

The intervention is such that blinding of allocation is not possible.

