# 9 ASSESSMENT OF SAFETY AND EFFECTIVENESS

## 9.1 Assessment of clinical effectiveness

SCRIP-score: Respiratory rate, heart rate and oxygen saturation are measured and scored in a table, need for respiratory support is part of the table. The average of total scores is analyzed.

HRV: Heart rate variability is measured for an appropriate interval, possibly using the "Faros 360" and analyzed according to Porges method by the Nurture Science Programme, Columbia University, NY. Average and median values are analyzed.

Respiration: Need for surfactant, number of days in ventilator, number of days in CPAP, number of days requiring supplemental oxygen collected from hospital case record. Proportions and median values will be analyzed.

Temperature: Axillary temperatures will be recorded. Average and median values are analyzed.

Infection: Proportion of infants experiencing sepsis during admission collected from hospital case record, as well as days receiving antibiotics. Average and median values are analyzed.

Breastfeeding and nutrition: Age at first feed, age at first passage of meconium, time to full enteral nutrition, lowest weight, time to removal of feeding tube, time to regained birth weight, weight gain in grams per day during hospital stay, weight at discharge and at term age is collected from the hospital case record. Breastfeeding status is determined from Index of Breastfeeding Status, Breastfeeding Self-Efficacy Questionnaire and Infant Breastfeeding Assessment Tool (IBFAT). A PhD student will be responsible for extracting data from case record (Take Care and Clinisoft). A research nurse will distribute questionnaires and parents will complete them during admission or at home prior to follow-up visits. Proportions are analyzed.

Epigenetics: Whole genome analysis as well as locus specific methylation of stress related genes for Oxytocin receptor (OXTR), glucocorticoid receptor (NR3C1), Arginine-vasopressin receptor (AVP), Proopiomelanocortin (POMC), Glutamate decarboxylase-1 (GAD1), Glutamate receptor (GRM1), Brain-Derived Neurotrophic Factor- (BDNF), serotonin transporter (SLC6A4 och SERT), serotonin receptor (5H2A) och serotonin degradation enzyme

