(MAOA) i cord blood postpartum, in buccal swabs postpartum. Midwife or nurse in labour ward collect cord blood concomitant with routine collection. Neonatal nurse collects blood samples at the same time as required clinically, as well as buccal swab during hospital stay or at follow-up visit. Samples are transported to the Unit for "Medicinsk Epigenetik, Centrum för Molekylärmedicin", KI. Analysis is undertaken by responsible researcher.

Microbiota: Infant microbiome colonization is identified with DNA analysis from fecal samples and skin swabs, and compared to that of their parents. Samples from infant are collected by ward nurse. Tests from parents are collected by nurse, or by the parents themselves. Samples are sent to the Center for Translational Microbiome Research (Molekylär- och Tumörbiologiskt Centrum; MTC).

Brain function maturation: EEG is measured with 8 leads using existing apparatus in clinical use. The results will be interpreted by the Nurture Science Programme, Columbia University, NY.

Structural maturation of brain: MR brain will be done on a subsample at term age. Results will be interpreted by radiologists.

Attachment: attachment will be assessed by psychologist on films made during the "Still Face-test" as well as the Parent-Child Early Relational Assessment Scale (PCERA). Filming is done by research staff. A psychologist or other appropriately trained staff at Linköping University or Karolinska Institutet will interpret the films.

Brain function: Functional magnetic resonance imaging (fMRI) will examine activation patterns in specific areas on mother's brain while she looks at pictures of her own and other infants in different moods. Parents will be invited to radiology department and the examination conducted by radiologists who will assess whether there are any structural differences, with the hypothesis that functional and structural connectivity in parenting behavior specific areas (e.g. prefrontal cortex and amygdala) are related to time in SSC.

Parental mental health: Experience of care will be assessed in interviews at discharge. Questionnaires Edinburgh Postnatal Depression Scale (EPDS), The Spielberg State-Trait Anxiety Inventory (STAI) and the Swedish Parenthood Stress Questionnaire (SPSQ) are administered. A research nurse distributes the questionnaires and parents complete them during hospital stay or at home before follow-up visit. Proportions are analyzed.

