Stress reactivity: Salivary cortisol levels measured in infant and mother. A clinical nurse takes the saliva sample during hospital stay or at follow-up. Samples not taken at visit (planned morning and night samples) are collected by parents and sent. Samples are collected at CMM and will later be sent to the University Hospital in Linköping for analysis by immunoassay. Co-variability in mother-infant tests will be analyzed.

Infant psychomotor development: Assessed by APIB; further as described in hospital case record at follow-up visit according to Infant Behaviour Questionnaire (IBQ) and Ages and Stages Questionnaire (ASQ), also developmental assessment according to Bayley Scales of Infant and Toddler Development 3rd Edition and Modified Checklist for Autism in Toddlers (MCHAT). PhD student will collect data from hospital case record. Parents complete questionnaires before follow-up visits. A psychologist will document developmental assessment in case record, a PhD student will collect this. Averages and proportions are analyzed.

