## **9.3 Assessment of results- effectiveness parameters**

Blood samples, buccal swabs, salivary samples, fecal samples, and skin swabs are taken by clinical staff and stored in the neonatal unit until transported to the CMM/KI (epigenetics), Linköping University Hospital, The Center for Translational Microbiome Research/MTC (microbiota). This includes also samples taken in Stavanger. All samples are encompassed by existing biobank regulations in each country, and authorization has been given. Clinical data is collected from hospital case record. Information on attachment, parental health and part of psychomotor development is collected from case record, other part from questionnaires and films. MR data is analyzed by neuroradiology specialists at Karolinska University Hospital and Stavanger University Hospital. Many outcomes are of a nature that reference values and detection limits do not apply, rather evaluation is by association studies and exploratory analysis.

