#### **14.4 Trial subject information and consent**

The research team (research nurse and PhD student) will screen antenatal and delivery ward admissions and communicate with clinical staff on potential preterm births. When a woman with threatening preterm birth is identified the information on the study will be provided verbally and in writing by the research team, but only after general information about preterm birth has been provided. When the parents (both, if present) have had opportunity to ask questions they will be invited to give consent, and subsequently sign consent forms. This will also be noted for the attention of neonatal ward staff, so that they are aware of this consent and potential research subject. The original consent form is archived, and the parents receive a copy.

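### The allocation arm is noted in the case record where the developmental examiner writes, and no assessor is masked: an avoidable risk of detection bias in Bayley and APIB

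*Protocol*

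**What the plan says.** Section 8.7 of the protocol disposes of blinding in one sentence: "The intervention is such that blinding of allocation is not possible". It does not mention outcome assessors.

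Section 13.1 describes most trial data as clinical information "which is found in the hospital case record, this is the primary data source". The same section requires a note in that record covering "participation in the study, the study name, the allocation arm, study ID number and contact persons for study".

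For the 24-month developmental outcome, section 9.1 states: "A psychologist will document developmental assessment in case record, a PhD student will collect this". Section 6.2 also takes psychomotor development from the case record at term age, 3-4 months, 12 months and 24 months. Section 7.2 places the APIB observation at the term-age follow-up visit or at a separate term-age visit.

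On infant MRI, section 9.1 says "MR brain will be done on a subsample at term age. Results will be interpreted by radiologists", and section 9.3 adds "MR data is analyzed by neuroradiology specialists at Karolinska University Hospital and Stavanger University Hospital". Neither says whether the readers see the case record or know the arm.

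The only text that approaches masking is the confidentiality paragraph in section 14.2. It promises analysis under a study ID once data have been collected.

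**The concern.** Parents and bedside staff cannot be blinded to skin-to-skin care, and section 8.7 is right about that. The reason does not extend to someone who scores a child at term age or at 24 months, or who reads an image. For those people masking is a matter of who is told what. The protocol plans nothing of the kind, and section 13.1 places the arm in the record in which one of these examiners works.

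Bayley and APIB depend on an examiner's judgement, so knowledge of the arm can shift scores, and a larger sample does not remove such a shift. Long-term neurodevelopment is part of the aim in the Summary, and Bayley is the only secondary outcome given its own sample size in section 11.3. Section 14.2 expects that ward staff may regard control care as inferior. That concerns ward staff rather than examiners, so it shows that such a belief is foreseen in the units but does not establish the direction of any bias.

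**Working it through.** The plan gives no figure on this point. The check is to follow the arm from the note to each assessor.

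1. **Where the arm sits.** Section 13.1: in the hospital record, in the same note as the study ID. Section 11.1 also says the study ID can be found in that record. A coded ID therefore masks only a reader who has no access to the record.

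2. **Who could meet it.**

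| Outcome | Assessor | Link to the record |
|---|---|---|
| SCRIP, first six hours (6.1, 7.2) | Direct bedside observation | Irrelevant; the place of care is visible |
| Bayley, 24 months (9.1) | Psychologist | Stated: the assessment is entered in the record |
| APIB, term age (7.2, 9.1) | Not named | Inferred: done at the hospital follow-up visit or a further term-age visit |
| Infant MRI, term age (9.1, 9.3) | Radiologists at the trial hospitals | Inferred only |
| EEG, HRV (9.1) | Outside university programme | None stated |
| Still Face and PCERA films (9.1) | Psychologist or trained rater at a university | None stated |
| Hospital-course data (9.1) | PhD student extracting from the record | Stated |

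3. **Whether another provision masks them.** The study-ID tagging in section 14.2 applies after collection. A Bayley or APIB score is fixed by then, so the provision does not mask the examination. It could help with recordings read off site, but it is not worded as a masking rule.

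4. **Whether extraction could be masked by changing the note.** No. Section 7.2 collects time in skin-to-skin contact and in other places of care at discharge, and sections 8.3 and 8.9 require it to be documented. Anyone handling those data would probably infer the arm. The same student role also recruits, under section 14.4: "The research team (research nurse and PhD student) will screen antenatal and delivery ward admissions". Masked extraction would need a second extractor or a split of tasks.

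5. **Size.** The documents contain nothing from which to estimate an examiner's shift. The following shows only how a shift would act. Suppose there is no true effect and a systematic shift of b SD between arms, with n per arm. Then SE = √(2/n), and the two-sided error rate at nominal 0.05 is 1 − Φ(1.96 − b/SE) + Φ(−1.96 − b/SE). The values of b are assumptions:

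| b (SD) | n = 52 (half of 104, section 11.3) | n = 75 (section 7.1) |
|---|---|---|
| 0 | 0.050 | 0.050 |
| 0.1 | 0.080 | 0.094 |
| 0.2 | 0.175 | 0.232 |
| 0.3 | 0.334 | 0.451 |

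For n = 75 and b = 0.1: SE = √(2/75) = 0.163 and b/SE = 0.61, giving 0.094. The error rate rises with n, which is why sample size does not protect against this bias. The table is not evidence that any shift occurs.

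**The case against.** A reader might infer that the plan unblinds its assessors. The documents do not support that. Section 13.1 does not say where in the record the note stands or who opens it. Section 9.1 has the psychologist write in the record, not read the neonatal part first. For MRI, access to the record is an inference from the readers' place of work. This objection stands, and the point is worded as a risk.

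A reader might also extend the point to EEG, HRV and film ratings, or hold that data extraction could be masked at no cost. No section gives the off-site readers the hospital record, and extraction fails for the reasons in step 4. Both extensions are dropped.

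Section 8.7 can be read as describing the intervention only, without denying that assessment could be masked. Section 13.2 also refers to more detailed operating procedures that are not at hand. That is fair, but the placement of the arm is a rule stated in this protocol, and a procedure written elsewhere would have to work against it.

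The strongest practical objection is that taking the arm out of the note achieves little alone. Parents know the arm and come to the visits, and skin-to-skin time may appear elsewhere in the record. This also stands in part. Much of the benefit comes from the instructions to parents and examiners, so the note should be changed together with those instructions.

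**Conclusion.** The point holds as an avoidable risk of detection bias. The protocol puts the allocation arm in the record in which the developmental examiner works, treats blinding as impossible without distinguishing caregivers from later assessors, and masks nobody. The exposure is documented for the 24-month developmental assessment. For APIB and infant MRI it rests on the inference that assessors at the trial hospitals can open the record.

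The primary SCRIP outcome is untouched. Questionnaires completed by parents and outcomes measured from samples are also outside the point. Neither the size nor the direction of any bias can be estimated from the documents. The change is worth making because it is cheap and protects a long-term outcome named in the trial's aim.

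**What to change.** - **Section 13.1:** limit the standing note to participation, study name, study ID and study contact. Hold the arm in the research file and on the neonatal bedside sheet.
- **Section 8.7:** confine the statement to parents and care staff. Add that Bayley and APIB examiners and MRI readers are not told the arm, and that off-site film, EEG and HRV readers receive coded IDs only.
- **Follow-up visits:** ask parents not to disclose the arm. Have the examiner complete scoring before opening the neonatal record, and record whether the arm became known and when. For children whose record already carries the arm, this order of work is the main safeguard.
- **Extraction:** state that it is done with knowledge of the arm.

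The cost is one record template, a few sentences of protocol text and an instruction to existing assessors, with no extra staff. There are two downsides. Follow-up clinicians who need the arm must ask the study contact. Masking will also be incomplete, so reports should give the number of assessments in which the arm became known.

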### 13.2 Monitoring

The conduct of the study is described in this protocol, and in more detailed written form as Standard Operating Procedures (SOPs). Investigator is responsible for all collaborators contact details, areas of responsibility, availability of CV's, and the delegation list. In Sweden the trial will be monitored by the Karolinska Trial Alliance (KTA) and sponsor is responsible for establishing a monitoring plan. Monitoring in Norway will be done in a similar way, though monitor is not yet appointed.

## 14 ETHICS

### 14.1 Ethics review board

Ethical approval for this study has been granted by ethics boards in Stockholm, Sweden and Stavanger, Norway.

### 14.2 Ethical conduct of the study

The study will be conducted according to this protocol, and according to GCP, and according to the declaration of Helsinki. All investigators and research staff will have GCP training.

Risk of hypothermia:

A pilot study (10) suggested that infants of this gestational age may run the risk of hypothermia when cared for in SSC. To ensure that infants allocated to intervention stay warm they will be carefully dried before they are placed on parent's chest, and then covered with warmed textiles. The very smallest and those requiring longer stabilization may start on the resuscitaire where adequate warmth is ensured while ventilation or CPAP is initiated. Should any infant in SSC become hypothermic despite the described measures, it will be placed in a warm incubator and then return to SSC only when temperature is normal.

#### Sudden Unexpected Postnatal Collapse:

Sudden Unexpected Postnatal Collapse (SUPC) has recently been highlighted: seemingly healthy full-term infants may become suddenly lifeless and require resuscitation (11). SUPC has been associated with unobserved SSC and unsupervised breastfeeding in primiparous mothers, in prone position, and exhaustion with lack of attention in parents. In our study we do not see any risk of SUPC, as these infants will be maintained in a safe position with a garment and will be constantly observed by research staff and monitored by pulse oximetry.

#### Poorer observation:

Infants in SSC need to be covered by a blanket or garment to ensure they stay warm. This may result in the ward staff not having the same visual oversight of the infant as they would in an incubator or cot. In this study infants as described above will be monitored electronically, and the care of small and unstable infants already includes regular and frequent checks of the infant's condition and vital signs. In addition, as parent is always near the infant and can indicate if all is not well.

#### Discomfort:

The intervention has been observed to provide comfort to preterm infants. Ward staff will however need to provide comfort to the parents, including the reassurance that it is not the parents' responsibility to monitor their infants, the parents should feel secure and not abandoned knowing they are not alone with their newborn unstable premature baby. Ward staff may also feel that the control group infants are receiving substandard care, as they have experience in providing SSC to infants born with higher gestational age. Blood sample collections in the study have been timed to coincide with necessary routine and clinically indicated blood sampling, with the exception of the 3–4-month sample and the 2-year sample that do require extra needling. Buccal swabbing and skin swabbing may be slightly uncomfortable for the infant and may predispose to mild anxiety when repeated later in the study.

#### Confidentiality:

The research team and the monitors will access the patient case records as part of the study. The research nurse and the investigator that does the screening of mothers for enrollment will also be examining case records before mothers give consent. Once data has been collected it will be tagged with a study ID so that all subsequent analysis is totally anonymous.

### **14.3 Risk benefit evaluation**

Infants in the control group will receive all care in accordance with current clinical best practice. Infants in the intervention arm may benefit from hypothesized advantages. All study subjects will receive additional follow-up compared to those not participating. This might be strenuous but can also provide additional comfort and reassurance that their infants are receiving extra care at the beginning of their lives and after discharge. It may provide them with increased opportunity to ask questions and an assurance that their infant has been fully investigated. If anything of significance is discovered during follow-up, immediate referral will provide early intervention support.

If we find positive short and or long-term benefits of the intervention, this will lead to a more equitable and evidence-based care than is currently provided. Should a potential risk be identified, this can be incorporated into care plans for better outcomes. On the other hand, if we find tangible risks with SSC provided to these very small and fragile infants, we will with this evidence base be able to stem the trend observed in many hospitals of giving more and more SSC to smaller and sicker babies without any evidence base of safety and effectiveness. There is also the risk that this form of care receives a tarnished reputation if not suitable for small and fragile infants, which

would make staff and parents afraid to provide SSC even on bigger and stable infants where the benefits are well established.

#### **14.4 Trial subject information and consent**

The research team (research nurse and PhD student) will screen antenatal and delivery ward admissions and communicate with clinical staff on potential preterm births. When a woman with threatening preterm birth is identified the information on the study will be provided verbally and in writing by the research team, but only after general information about preterm birth has been provided. When the parents (both, if present) have had opportunity to ask questions they will be invited to give consent, and subsequently sign consent forms. This will also be noted for the attention of neonatal ward staff, so that they are aware of this consent and potential research subject. The original consent form is archived, and the parents receive a copy.

### **15 DATA MANAGEMENT AND ARCHIVING**

#### **15.1 Case Report Forms**

All data to be analyzed will be entered into a CRF, by the research nurse or by the PhD student, later the principal investigator will verify and sign. Should any changes be made, this should be signed off by the person making them, and a reason provided. Once all data is entered, verified, and signed off the file will be locked and cannot be changed further.

